
#### Control group

The family caregivers of the control group will receive only a portfolio of aftercare recommendations that are adapted to the individual situation of the respective family carer at the end of rehab. This recommendation will be self-implemented and is not accompanied by any aftercare measurement. Between T1 and T2, they will continue with their usual activities or on-site services at home, without restriction (usual care).

### Effect evaluation

To evaluate the intervention effects, quantitative measurements will be applied. The measurements were chosen based on their appropriateness for the scientific issues, the target intervention, sample, data collection procedure (written survey) and psychometric properties. Table 1 summarizes all core measurement instruments to be used in this study.

**Table 1 Tab1:** Core set of used instruments

Dimensions	Measurement Instrument	t_0_	t_1_	t_3_	t_4_
*Primary Outcome*					
Participation	Index zur Messung von Einschränkungen der Teilhabe (IMET) [19, 24]	●		●	●
*Secondary outcome*					
Psychological distress n	Center for Epidemiological Studies-Depression (CES-D) [27]	●	●	●	●
General health complaints	Symptom Checklist 90 Revised (SCL-90-R) [28]	●	●	●	●
Subjective health–related quality of life	World Health Organization Quality of Life-BREF (WHOQUOL-BREF) [29, 30]	●	●	●	●
Social support	Fragebogen zur sozialen Unterstützung (F – SozU) [31]	●		●	●
Performance in different areas of life	Single scales [32, 33]	●		●	●
Support offers	Single items	●		●	●
*Moderator variables*					
Height, weight, smoking	Single items [34]	●		●	●
Socio-demographic data	Deck & Röckelein 1999 [35]	●		●	●

#### Primary outcome

Participation restrictions are recorded using the index for the measurement of restrictions on participation (Index zur Messung von Einschränkungen der Teilhabe, IMET [19, 24]). This determines, using ICF criteria [25], the subjective impairment of chronically ill people in their everyday lives. It captures restrictions on participation in nine areas relevant to everyday life on a scale ranging from 0 to 10 and can be evaluated both at the individual item level and as a total score. High values indicate high participation restrictions. The IMET has proven to be valid and reliable for application in chronically ill patients [19, 26].

#### Secondary outcomes

Depressed mood states are measured with the German version of CES-D, which contains 20 quadruple scaled items. The presence and frequency of depressive symptoms are thus tested for. The evaluation is performed through a sum score, which can reach a maximum value of 60 points. A higher value describes a stronger expression of depressive symptoms. Good reliability and validity are reported [27].

For the general complaints, the subscale of somatization from the Symptom Checklist by Franke (SCL-90R) is used. This scale captures subjective impairment due to physical complaints via 12 five-fold stepped items. High values indicate high impairments. The reliability and validity of the scale have been proven [28].

The WHOQOL-BREF is used to assess the generic subjective perceived quality of life of the family carers. It contains 26 items on four dimensions; high values indicate a high quality of life. It is a valid and reliable cross-indication measuring instrument for assessing the quality of life [29, 30].

The extent of social support is assessed with the questionnaire for social support (FSozU K22). It contains 22 items; high values indicate a high level of social support. High reliability and validity have been proven [31].

Performance in the areas of life, everyday life, leisure and job, are captured on three numerical scales ranging from 0 to 10, with high values indicating high performance. In routine data collection, the three items have been proven to be a valid method of determining performance limitations [32, 33].

The utilization of support services will be recorded by single items used in a recent study on the rehab of carers. There will be standardized queried, inter alia, nursing service, self-help groups, household help, pastoral care and use and type of other offerings.

Moderator variables, risk factors [34] and socio-demographic variables [35] will also be recorded.

### Process evaluation

Items for process control, feasibility and satisfaction address the feasibility and acceptance of the intervention strategy by rehabilitants and staff. For this purpose, different single items (five-tier Likert scales) are used, which were developed and used in comparable studies [18].

In terms of the process control, the short structured evaluation forms completed by the participants after each telephone-based aftercare group are first sent to the moderator, who can use this information to form the next aftercare group session. For the evaluation of the process quality over the course of the intervention, the structured evaluation forms and all documentation records of each telephone-based aftercare group session (immediate and memory protocols) are evaluated in the ISE after the end of intervention. The experiences of the family carers with the telephone-based aftercare groups are requested during interviews at the end of the intervention and 6 months after the end of the intervention (*N* = 16). The focus here is particularly on the personal benefits and the temporal feasibility of the telephone-based aftercare groups, the satisfaction with these groups and the group composition. In addition, the wishes and needs of the participants or carers, respectively, are recorded, with regard to the further development or optimization of the telephone-based aftercare groups. To ensure the most heterogeneous sample composition, participants with different characteristics of the variables gender, education and time load in hours/day for the care of the family member with dementia are recruited for the interviews [36]. In addition, there will be a focus group discussion with the participating moderators of the telephone-based aftercare groups at the end of the intervention. Here, the feasibility aspects and the possibilities for further development will be focused on.

### Health economic evaluation

As part of the health economic evaluation, a cost-benefit analysis is performed. The EQ-5D 3 L is used to determine the values in use [37]. To calculate the index, the tariff, according to Greiner et al., is used as a guide [38]. When recording the costs, it is assumed that the costs of rehab are the same in both groups and, thus, only the costs of the intervention are relevant. In the health economic evaluation, therefore, the additional costs for the intervention are compared with the possible improvements in the utility values.

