
The temporal and organizational procedure of the Talking Time – REHAB aftercare measurement consists of the following four components.**At the end of rehab – inclusion and preparation.** At the end of the rehab stay, a social worker, who is familiar with German social security statute book XI (Sozialgesetzbuch, SGB XI) and responsible for the moderation of the aftercare groups, compiles a portfolio of aftercare recommendations that are adapted to the individual situation of the respective family carer. These recommendations largely refer to possible strategies, as well as the individual situation of the carer, offering meaningful support but also providing recommendations for self-care in daily life, including nursing and supporting. The aftercare recommendations are discussed with the family caregivers at the end of rehab. In this discussion, the appointments of the telephone-based aftercare groups will be determined, and conversational rules for the groups are discussed. The rehabilitant receives a written checklist with all important information, including the conversation rules and the group folder (see below), to take home.**Reminder call**. The moderator calls each rehabilitant of the aftercare group 1 day before the next scheduled appointment. Such a reminder call lasts approximately 3–5 min and is necessary because, with a one-month interval of the aftercare group, the next appointment may be lost or forgotten by the participants.**Structured telephone-based aftercare groups**: Overall, the intervention provides for participation in six telephone-based aftercare group sessions within 6 months (every 4 weeks), each lasting approximately 60 min. The groups consist of a maximum of five caregivers and a moderator, who leads the group, and the groups are closed; the participants in a telephone-based aftercare group remain constant over the period of the six appointments. These groups are conducted as dial-out telephone conferences using a telephone computer system. The participants and the moderator are simultaneous automatically called by the telephone computer system and are connected to one another in the virtual conference room, after they have confirmed their personal receipt of the call by pressing the ‘1’ key of the dial pad of their telephone. In this manner, the telephone computer system confirms that an answering machine has not accepted the call. At the beginning of each group discussion, each participant gives a short update on his individual care and support situation and the status of the implementation of his aftercare recommendations. Afterwards, in all sessions, except for the first one, one of five themes will be introduced by the moderator: 1.) aftercare, implementation of the aftercare recommendations developed during the rehab; 2.) dealing with the relative with dementia; 3.) self-care (What am I doing for myself? When and where can I draw strength?); 4.) ambiguous loss, coping with grief and loss in dementia; and 5. social networks, perception and use of networks. To support the thematic introduction of each support group, each participant will receive a group folder developed particularly for the Talking Time – REHAB study, summarizing information on the themes of the Talking Time – REHAB sessions and including a checklist regarding technical issues (e.g., ‘what is the battery status of my telephone?’), which must be considered prior to each group session. The group folder can also be used as a workbook (e.g., for notes) during the support group meeting. This initial round, including impulse presentation, should take approximately 10–15 min. The remaining 45 to 50 min are available for the moderated exchange of experiences and the discussion between family carers. At the end of the group discussion, the moderator summarizes the content of each session. For quality assurance, the moderator is supervised by a psychological psychotherapist after the third and sixth session of the respective aftercare group.**Follow-up work of telephone-based aftercare groups**: Each group discussion is evaluated by each participant in writing. Before leaving the rehab facility, the participants receive a structured evaluation form for each aftercare group appointment. Using this form, family carers are encouraged to think about and evaluate each telephone group session (e.g., regarding the relevance of the topic of the session, open questions, helpfulness of the meeting, moderation of the group, well-being in the group or implementation of aftercare recommendations, etc.) The form is sent back to the moderator immediately after the telephone group session and provides the basis for the preparation of the next telephone group, but can also help in the sense of a formative process evaluation (see below, section on ‘process evaluation’) to optimize the behaviour of the moderator in the group situation. At the end of the intervention, as part of the summative process evaluation, all questionnaires will be sent to the ISE.

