#### Health economic analysis

Within the cost-utility-value analysis for the utility value, which is collected at three measurement times, the area under the curve (AUC) is calculated separately for IG and CG. The difference in the AUC values between IG and CG describes the difference in the quality-adjusted years of life. This difference is contrasted to the difference in costs.

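### Equal rehab costs do not justify leaving post-rehab service use out of the cost comparison; the incremental cost is incomplete to the extent that service use differs between the groups

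*Protocol article*

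**What the plan says.** All references are to the Protocol article.

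- **Health economic evaluation** fixes the cost scope and gives its reason: "it is assumed that the costs of rehab are the same in both groups and, thus, only the costs of the intervention are relevant". It then states the comparison: "the additional costs for the intervention are compared with the possible improvements in the utility values".
- **Health economic analysis** takes the difference in area under the utility curve as the difference in quality-adjusted life years and continues: "This difference is contrasted to the difference in costs". It adds no further cost item.
- **Design** places randomisation at the end of rehab, with follow-up at 6 and 12 months.
- **Intervention group** has participants report at each session on how far their recommendations have been put into practice. Two of the five themes are "aftercare, implementation of the aftercare recommendations developed during the rehab" and "social networks, perception and use of networks".
- **Control group** gives controls an individual portfolio of recommendations to carry out on their own. Between the end of rehab and the 6-month follow-up "they will continue with their usual activities or on-site services at home, without restriction (usual care").
- **Secondary outcomes** states: "The utilization of support services will be recorded by single items used in a recent study on the rehab of carers". The listed services include "nursing service, self-help groups, household help, pastoral care and use and type of other offerings". Table 1 marks these items at baseline and at both follow-ups.

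**The concern.** The stated premise concerns costs incurred before randomisation. The conclusion drawn from it concerns all costs, including those of the following 12 months. Equal rehab cost removes one item from the comparison and leaves open whether later costs are equal.

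The omitted item is one that the aftercare could plausibly affect. The groups accompany carers in carrying out recommendations that controls implement alone, and the moderator is a social worker with knowledge of long-term-care insurance law. The trial also treats use of support offers as an outcome to be compared, while the economic section in effect sets the difference to zero.

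What is at stake is the cost per QALY. It would be too low if the intervention group takes up more paid support and too high if the groups avert such use. The article intends to establish the offer at the clinic after a successful evaluation, so the figure may inform that decision.

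**Working it through.** The article gives no intervention cost, no unit cost and no expected utility gain, so there is no economic figure of its own to reproduce. The check has three parts.

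**1. What the rule leaves out.** Let C be the intervention cost per carer, and S_IG and S_CG the mean cost of services used after rehab in each group.

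- Full incremental cost = C + D, where D = S_IG − S_CG.
- Cost under the plan's rule = C.
- The rule is therefore off by D, and it is correct only if D = 0. No section states or argues that D = 0, and no section states a perspective under which D would be irrelevant.

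**2. How large the counted cost is.** Inputs from the section Intervention group: six sessions of about 60 minutes, a reminder call of about 3 to 5 minutes to each carer before each session, and at most five carers per group.

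- Sessions: 6 × 60 = 360 minutes per group.
- Reminder calls in a full group: 6 × 5 × 3 = 90 to 6 × 5 × 5 = 150 minutes.
- Per carer: (360 + 90) / 5 = 90 minutes to (360 + 150) / 5 = 102 minutes, or 1.5 to 1.7 hours.
- With three carers per group (assumption): 360 / 3 + 18 to 30 = 138 to 150 minutes, or 2.3 to 2.5 hours.

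This is moderator contact time only. Preparation, supervision after the third and sixth sessions, the group folder and the telephone conference system come on top, so the figure is a floor for C.

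**3. How far D could move the result.** The values here are assumptions chosen only to show the mechanism: C = 200 euros and a gain of 0.02 QALY.

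| D (euros per carer) | C + D (euros) | Result at 0.02 QALY |
|---|---|---|
| −300 | −100 | net saving of 100 euros per carer |
| −100 | 100 | 5,000 euros per QALY |
| 0 (plan's rule) | 200 | 10,000 euros per QALY |
| +100 | 300 | 15,000 euros per QALY |
| +300 | 500 | 25,000 euros per QALY |

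With an assumed gain of 0.01 QALY, the plan's rule gives 20,000 euros per QALY and D = ±100 gives 10,000 or 30,000. With 0.05 QALY, the figures are 4,000 and 2,000 or 6,000. In each case a D of half of C changes the ratio by half, and a saving larger than C reverses the sign of the incremental cost.

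**The case against.** **Perspective.** Cost scope depends on perspective, and a condensed article may leave that to a fuller document. The Discussion speaks of a small additional expense at the clinic, and the Background shows that costs can fall on different insurers. A narrow analysis of intervention cost per QALY can be legitimate. This stands as a defence of a narrow scope, and the fix allows for it. It does not rescue the text as written, because the article justifies the exclusion by equal rehab costs and not by a perspective.

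**A difference is not established.** A reader might infer that the plan's own hypotheses imply unequal service use, so that the incremental cost is simply wrong. The documents do not support this. The stated hypotheses concern social participation and the maintenance of health effects and competences. Support offers are a secondary outcome with no predicted direction. Both groups receive individual recommendations, so uptake prompted by these alone is common to both. The theme on networks is not said to mean nursing service or household help.

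**Contact time is not the whole cost.** It is also tempting to read 1.5 to 1.7 hours as everything the plan counts, so that a few hours of paid support would exceed it. That fails, because the figure omits several components and assumes full groups.

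**Data limits.** Baseline surveys began in June 2018, so a frequency question added later would miss earlier questionnaires. The article does not say whether the single items record quantity or a recall period. This objection stands and limits how precise any costing can be.

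**Conclusion.** The point holds in a conditional form. The stated reason does not support excluding post-rehab service costs, and the cost difference is incomplete by exactly the difference in service use between the groups. The documents fix neither the size nor the direction of that difference, and it could be zero. That a modest difference could be material rests on the low contact time per carer and on the illustrative euro and QALY values above, which are assumptions. This is a stated rule and not a detail left for later, so it should be changed. It concerns only the economic evaluation.

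**What to change.** 1. Delete the inference from equal rehab costs to intervention costs only.
2. Define the incremental cost as intervention cost plus the difference between the groups in post-rehab service use to 12 months. Value the support-offer items from the 6- and 12-month questionnaires at standard unit costs as far as they record quantity. Where they record only yes or no, state the assumed volumes and show a range.
3. Report the intervention-only result alongside.
4. If the items cannot support costing, state the narrow perspective, label the result as intervention cost per QALY, and report service use by group next to it.

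The cost is some extra analysis work and the sourcing of unit costs. It needs no additional visits or questionnaires. The drawback is that service volumes will be approximate where frequency was not collected.

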### Data management

#### Documentation in the rehab facility

For the organization and documentation of the flow of participants in the participating rehab facility, an automated documentation (Excel file) will be created. Staff responsible for recruitment in the rehab facility will be trained to use this file before the beginning of the study. For the consecutive numbering of enclosed subjects, each participant will be assigned a three-digit identification number (ID) (pseudonymization of data). All personal data will be documented on a separate data sheet in the Excel file; a corresponding link is made via the ID. Before transferring the data to the ISE, the personal information will be deleted. The collection of these data for standardized documentation is carried out exclusively in the participating rehab facility. Data generated by means of questionnaires will be collected and stored separately.

#### Data entry

Questionnaire data will be entered by a student assistant under the guidance of a research associate. Once the data have been entered, they will be checked for validity and plausibility by random double entries (5–10%).

### Data analysis

#### Effect analysis

For the effects analysis of the longitudinal data, analysis of variance with repeated measurements is used; for nominal and ordinal scaled parameters, contingency table analyses are used; and for subgroup analyses, chi-square tests and t-tests are used. The analyses are performed with SPSS 22.0 and complete cases will be analysed.

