## Methods

### Design

To investigate the long-term effects of telephone-based aftercare groups, a randomized controlled prospective longitudinal study is being conducted at one rehab centre. For the effect and process evaluation, in the sense of a mixed-method approach, both quantitative and qualitative methods are used [17]. Rehabilitants receive specific rehab for family carers of people with dementia and are randomized at the end of the measure. The randomization is performed externally by the Institute for Social Medicine and Epidemiology (ISE) of the University of Lübeck by generating a randomization list with the statistics program SPSS 22.0. After the rehab, at six appointments and in addition to the aftercare recommendations by the social worker, the intervention group receives telephone-based aftercare in groups, and the control group receives only the aftercare recommendations. The study design includes four measurement times: at the beginning (t0), at the end of the rehab (t1), 6 months after the end of the rehab (for the IG after completion of telephone-based aftercare groups) (t2) and 12 months after rehab ends (t3). Figure 1 represents the study flow.

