### Sample size calculation

As no studies in the field of nursing care have investigated the effects of aftercare in addition to a supportive intervention for carers, the sample size calculation for this study is based on the current results of the evaluation study on the effectiveness of the rehab program for family carers of people with dementia without aftercare (“standard care”), upon which this study project is based [11], and the results of a 2012 study of the impact of individualized aftercare on long-term rehab effects [18].

In the study with family carers, six months after rehab ended, the outcome parameter of participation, which was captured with the Index for the Measurement of Restrictions on Participation (Index zur Messung von Einschränkungen der Teilhabe, IMET [19]), showed that the rehab effect had nearly completely disappeared (ES = 0.06).

In the rehab aftercare study for the indication lower back pain, the same effect was observed for participation (IMET) in the CG [18], while the rehabilitants of the IG with individualized aftercare still showed an approximately medium effect size after 12 months (ES = 0.44).

Due to the consistently strong effects at the end of rehab in most recorded outcomes in the evaluation study for the rehab program in Ratzeburg, we expect for this controlled study, with telephone-based aftercare at the 6-month follow-up, an average effect of ES = 0.5 in the IG and a small effect of ES = 0.06 in the CG. Using a test power of 80% as the base, a two-sided t-test with an alpha error level of 5% requires a net group size of *N* = 82 each for the IG and CG. Based on experience with the current evaluation study of the rehab program in Ratzeburg and due to the high degree of loyalty of the rehabilitants to the rehab facility, we assume a moderate dropout rate of 20%. To evaluate *N* = 82 rehabilitants per group, initially, 103 participants per study group should be included. The rehab centre treats between 210 and 330 carers per year. The required number of cases can thus be achieved within the envisaged recruitment time.

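### The stated 80% power is for a 6-month t-test on IMET, not for the repeated-measures ANOVA planned as the effect analysis

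*Protocol article*

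**What the plan says.** The section on sample size calculation ties the expected effect to one time, "with telephone-based aftercare at the 6-month follow-up", and sets it at "an average effect of ES = 0.5 in the IG and a small effect of ES = 0.06 in the CG". It continues: "Using a test power of 80% as the base", "a two-sided t-test with an alpha error level of 5% requires a net group size of" 82 in each arm. With 20% dropout this becomes 103 recruited per arm.

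The section on effect analysis states: "For the effects analysis of the longitudinal data, analysis of variance with repeated measurements is used". It assigns t-tests to subgroup analyses, together with chi-square tests, and says that complete cases are analysed. It names no model term, contrast or time point.

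Table 1 marks IMET in its first, third and fourth columns, and not in the second, which is the end of rehab. The table heads its columns t0, t1, t3 and t4, whereas the design section runs from t0 to t3. Column order and the four-point schedule support reading the IMET waves as pre-rehab, 6 months and 12 months. On timing of allocation, the design section says: "Rehabilitants receive specific rehab for family carers of people with dementia and are randomized at the end of the measure". The abstract and the primary outcome section name IMET as primary without attaching a time to it.

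**The concern.** The sample size answers one question: do the arms differ in IMET at 6 months? A repeated-measures ANOVA over three waves puts a different question to the data. Its group-by-time test has 2 degrees of freedom and asks whether the difference between arms changes anywhere across pre-rehab, 6 and 12 months. It can be significant because of the 12-month wave alone.

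Two things are at stake. A null result could not be read against the stated 80%, because that figure describes another test. A positive result would leave open which follow-up carries the claim, although the sizing points to 6 months.

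**Working it through.** **Inputs from the article.** Effect sizes 0.5 and 0.06, so d = 0.5 − 0.06 = 0.44; two-sided alpha 5%; power 80%; 82 per arm; dropout 20%; IMET at three waves.

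**Assumptions.** The 0.44 is in units of the SD of an IMET score (the article does not say which SD). The correlation r is the same between any two waves (compound symmetry), from 0.3 to 0.7. The true difference is 0 before rehab, because allocation comes later, and 0.44 at 6 months. At 12 months it is none, half or all of 0.44.

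**Step 1: the article's own figure.** n = 2(1.960 + 0.842)² / 0.44² = 15.70 / 0.1936 = 81.1, so 82 per arm. The exact noncentral t gives 79.97% power at n = 82. For dropout, 82 / 0.8 = 102.5, so 103. Both figures reproduce.

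**Step 2: the group-by-time F-test.** The noncentrality is λ = (n/2) · Σ(δₜ − mean δ)² / (1 − r), with 2 and 324 degrees of freedom.

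- Full effect kept, δ = (0, 0.44, 0.44): the sum of squares is 0.1291. At r = 0.5, λ = 41 × 0.1291 / 0.5 = 10.6 and power is 83%.
- No effect at 12 months, δ = (0, 0.44, 0): the sum is again 0.1291, so power is the same.
- Half kept, δ = (0, 0.44, 0.22): the sum is 0.0968. At r = 0.5, λ = 41 × 0.0968 / 0.5 = 7.9 and power is 71%.

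**Step 3: a 6-month contrast adjusted for the pre-rehab score.** The effective standardised difference is d / √(1 − r²). At r = 0.5 this is 0.44 / 0.866 = 0.508, and power is 90%.

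| r | Group-by-time F, 12-month effect none or full | Group-by-time F, 12-month effect half | ANCOVA at 6 months |
|---|---|---|---|
| 0.3 | 69% | 55% | 84% |
| 0.4 | 76% | 63% | 86% |
| 0.5 | 83% | 71% | 90% |
| 0.6 | 91% | 81% | 94% |
| 0.7 | 97% | 91% | 97.5% |

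ANCOVA has the higher power in every row. At r = 0.8 the choice no longer matters for power: the F-test has 98% or more and ANCOVA 99.7%.

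**Step 4: what a significant F-test shows.** With a difference at 12 months only, δ = (0, 0, 0.44), the sum of squares is once more 0.1291. Power is 69%, 83% and 97% at r = 0.3, 0.5 and 0.7, exactly as for a difference at 6 months only. The F-test cannot tell the two situations apart.

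**The case against.** The strongest reply is that sizing and analysis may be closer than they look. The effect sizes in the sample size section describe how much of the rehab effect remains in each arm, so they can be read as change from pre-rehab. In a repeated-measures ANOVA restricted to pre-rehab and 6 months, the group-by-time test is the same as a t-test on change scores. Under the assumptions above that test has 66%, 80% and 95% power at r = 0.3, 0.5 and 0.7. This stands as a possible reading, but the article does not restrict the ANOVA to those two waves, and Table 1 supplies a third.

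It can also be said that an article need not list every term and contrast, and that an analysis plan may define them. That is fair, and silence on such details is not the point here. The article names one test to justify the sample size and another for the effect analysis, and those two statements have to agree.

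A reader might go further and infer that the trial is underpowered. The documents do not support that: the interaction test exceeds 80% in several of the cases above, and the inputs that decide it are not given. Nor does the article say that an overall F-test or the group main effect decides the trial, or that differences at single times will go unreported. The 6-month target is at least visible in the sample size section.

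Finally, with allocation after the pre-rehab measurement, a group-by-time analysis is a valid comparison. The preference for ANCOVA rests on precision and on matching the sized question.

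**Conclusion.** The mismatch is real. The 80% power and the 82 per arm belong to a 6-month two-sample t-test, and the planned repeated-measures ANOVA is a different test whose power is not stated. Under the stated assumptions its group-by-time test lies between about 55% and 97%. A loss of power is possible but not established. What does not depend on r is that a significant group-by-time result, taken alone, leaves the 6-month question unanswered.

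This is a clarification well worth making. It does not show that the design fails or that the planned analysis is biased. The sample size arithmetic is correct. The result rests on reading the IMET waves as pre-rehab, 6 and 12 months and, for the power figures, on compound symmetry and the assumed 12-month effect.

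**What to change.** Name one primary analysis: the difference between arms in IMET total score at 6 months after rehab, two-sided 5%, from ANCOVA with the pre-rehab (t0) IMET score as covariate. The same contrast from a longitudinal model adjusted for that score would serve equally. Make the 12-month contrast and the overall group-by-time test secondary. Say in the sample size section that the 82 per arm refers to this 6-month contrast.

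For CES-D, SCL-90-R and WHOQOL-BREF, which are also measured at the end of rehab, the scores taken before aftercare starts may likewise serve as covariates. That is a gain in efficiency and corrects no bias.

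The cost is a few sentences, settled before outcomes are compared by arm. The data, software and number of participants stay as they are.
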